### Process evaluation

Feasibility and acceptability of our outcome measures will also be determined by gaining the perspectives of family carers who took part in the intervention arm. Semi-structured interviews will be conducted post intervention (see Table 1) and held via a secured online platform, and interviews will be recorded, transcribed verbatim, and subjected to thematic analysis [29]. The interview schedule was developed to explore ways to make improvements to the Carers-ID intervention. Questions focused on the overall experience, relevance, usefulness, and potential impact of the intervention. For example, ‘What improvements do you think could be made to the Carers-ID programme?’ and ‘What has been the impact of the Carers-ID online programme on you and/or your family?’

### Procedures

Ethical approval has been granted by a university ethics committee at the lead authors institution (MHLS 23_04). Participants will be required to give informed consent before commencing the study. Participants will be asked to complete the psychometrically validated questionnaires at three time points: prior to taking part in the intervention, baseline measurement (T_0_), 2 weeks following baseline/completion of intervention (T_1_), and 3 months after baseline(T_2_). Semi-structured interviews will be conducted, as part of the process evaluation, with 12 participants to determine acceptability and feasibility of the outcome measures and the intervention.

Random allocation to the intervention and control conditions will be undertaken by an independent third party not involved with the research. The allocation ratio used will be 1:1. Random sequences will be generated using the Random.org (https://www.random.org/lists/) online service which uses atmospheric noise to ensure randomness. This will ensure members of the research team will be blind to allocation to reduce selection bias. Participants will complete the psychometric measures online with no data collection by members of the research team. Blinding of the research team to outcome assessment should have the effect of reducing detection bias. All participants will receive the intervention with those in the control group receiving this at a later stage. Due to the difference in timings, participants may become aware of group allocation.

### Data analysis

All analysis will be conducted on an ‘intention-to-treat’ basis. Participants’ data will be analysed based on the group to which they have been assigned, irrespective of attrition. IBM SPSS Statistics 27 software will be used to analyse the data.

A CONSORT diagram will outline the number of participants who were identified, recruited, commenced and finished the intervention, with recruitment rate reported as a percentage. Reasons for refusal and dropout during the intervention will also be recorded and reported. Descriptive statistics will be used to present baseline characteristics and feasibility outcomes. Inferential statistics (correlations and analysis of variance — ANCOVA) will be used as indicators of difference between the intervention and control arms and correlation between baseline and follow-up measurements. We will use data from this study, together with that from previous research, to inform a suitable sample size for a future effectiveness trial.

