### Participants and recruitment

Based on previous studies [19, 20] and best practice guidelines [19, 21] we estimate, we will need to recruit between 100 and 120 family carers who will be randomised to receive the intervention (*n* = 60) or assigned to a wait-list control (*n* = 60) group. The sample characteristics will be similar to the target population of the future large-scale effectiveness trial. Participants will be UK adults > 18 years of age and will be caring for a family member with an ID (people with all levels of ID). As this is a feasibility trial, the sample size is not intended to detect a statistically significant difference. However, these numbers will be sufficient to allow us to test the trial methodology and acceptability and feasibility of our psychometric measures [22, 23]. Data gained from this study will allow us to calculate a sample size for a future effectiveness trial.

Participants will be recruited through our voluntary sector partners. Letters of invitation and information sheets will be sent out to members of our partner organisations to inform them of the study trial. Those interested in taking part will contact the research team if they require further information or to indicate their wish to participate.

For the process evaluation, participants (*n* = 12) who have taken part in the intervention arm of the study will be invited to participate in an online interview. An invitation letter and information sheet will be sent to all participants in the intervention group by the researcher. Those interested in taking part will contact the research team if they require further information or to indicate their wish to participate.

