### Outcomes and success criteria

#### Primary outcomes

Criteria to assess the feasibility of progressing to a large-scale effectiveness trial include the following:Acceptability and feasibility of the outcome measures (completed by > 80% of family carers)Sufficient recruitment (> 90 carers) and participation and retention rates (> 80% of family carers)Effect sizes and estimate of variability (standard deviation), along with data from previous studies, may inform a sample size for a future effectiveness trial.

The primary outcome of this trial is to determine the feasibility of conducting a future effectiveness trial of the Carers-ID intervention, including acceptability and feasibility of the outcome measures, recruitment, participation and retention rates and effect sizes and estimates of variability.

Data on numbers of participants identified, recruited, commenced and finished in the intervention will be collected throughout the study. Reasons for declining participation and reasons for drop out will be recorded where possible. Feasibility of using the stress, anxiety, depression, resilience and well-being outcomes will be assessed through number of participants completing pre, post and follow-up measures. Acceptability of measures will be assessed qualitatively through semi-structured interviews (see below). We will also collect data on participant’s activity within the online intervention, including total time spent on the intervention and number of modules accessed, to enable us to assess intervention engagement and adherence.

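### Intention-to-treat is promised whatever the attrition, but the only between-arm method named, ANCOVA, cannot by itself use carers without a follow-up score

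*Protocol article*

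**What the plan says.** All of this is in the protocol article.

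- **Population (Data analysis):** "All analysis will be conducted on an ‘intention-to-treat’ basis", with data "analysed based on the group to which they have been assigned, irrespective of attrition".
- **Method (Data analysis):** "Inferential statistics (correlations and analysis of variance — ANCOVA) will be used as indicators of difference between the intervention and control arms". On software: "IBM SPSS Statistics 27 software will be used to analyse the data".
- **Time points (Design, Table 1, Procedures):** baseline (T0), 2 weeks (T1) and 3 months from baseline (T2), all completed online by the carer.
- **Size (Participants and recruitment):** the plan is to "recruit between 100 and 120 family carers who will be randomised to receive the intervention" or a wait-list control, 60 per arm at the upper figure.
- **Feasibility criteria (Primary outcomes):** "Sufficient recruitment (> 90 carers) and participation and retention rates (> 80% of family carers").
- **Use of the estimates (Primary outcomes):** "Effect sizes and estimate of variability (standard deviation), along with data from previous studies, may inform a sample size for a future effectiveness trial".

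The article does not give the ANCOVA covariates or say which follow-up it applies to. It mentions neither imputation nor complete-case analysis.

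**The concern.** Two questions are run together here. Keeping each carer in the assigned arm is a rule about grouping, and ANCOVA can honour it. Keeping carers in the estimate despite attrition is a rule about inclusion. ANCOVA cannot honour that alone, because it needs the outcome score. It also has no place for a T1 score when T2 is missing, although T1 is collected and may predict both T2 and who is lost.

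Unequal loss is plausible. Only the intervention arm is asked to work through 14 modules in two weeks, while controls gain access only after T2. What is at stake is the effect size taken towards the next trial's sample size. No efficacy conclusion depends on it, since the article says the trial is not sized to detect a difference.

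**Working it through.** The article gives no alpha, power, effect size or SD, so it has no figure of its own to reproduce.

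**1. How many carers can be missing.** Retention must exceed 80%.
- Of 120: 96/120 = 80.0% fails and 97/120 = 80.8% passes, so up to 120 − 97 = 23 may be lost.
- Of 100: 81 must remain, so up to 19 may be lost.

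These are carers without the score. A carer who stops the modules but answers the questionnaire stays in the ANCOVA, in the assigned arm.

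**2. Simulation with no true effect.** From the article: 60 per arm, three time points, pooled retention just above 80%. Assumed, and not in the article: normal scores with SD 1 (higher = more distress), the correlations below, and T2 dropout that rises with T1 distress in the intervention arm only. Retention is 71% vs 91%, pooled (0.71 × 60 + 0.91 × 60)/120 = 81%, which passes the criterion. There were 4000 runs per row. ANCOVA regresses T2 on arm and T0 in carers with T2. The comparator is a likelihood-type estimate that also uses T1. Negative values are a spurious benefit, in SD.

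| Correlations T0–T1, T0–T2, T1–T2 | ANCOVA | Using T1 |
|---|---|---|
| 0.7, 0.6, 0.7 | −0.070 | 0.001 |
| 0.5, 0.5, 0.7 | −0.115 | −0.002 |
| 0.6, 0.5, 0.8 | −0.127 | 0.000 |

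Slightly stronger dropout (retention about 70% vs 91%) gives ANCOVA biases of 0.08, 0.13 and 0.14 SD, and 0.00 in each row when T1 is used. Standard errors are 0.166, 0.174 and 0.176 for ANCOVA against 0.164, 0.170 and 0.171. A steep slope of 1.5 logits per SD gives 0.10 to 0.17 SD for ANCOVA.

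**3. Why it happens.** After adjustment for T0, the covariance of T1 and T2 is r12 − r01 × r02.
- Row 1: 0.7 − 0.7 × 0.6 = 0.28
- Row 2: 0.7 − 0.5 × 0.5 = 0.45
- Row 3: 0.8 − 0.6 × 0.5 = 0.50

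Dividing each bias by this gives 0.070/0.28 = 0.25, 0.115/0.45 = 0.26 and 0.127/0.50 = 0.25. So the bias is about a quarter of the part of the T1–T2 association that baseline does not explain. Adjusting for T0 removes the rest.

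**4. Other dropout patterns, ANCOVA, no true effect.**
- Random, about 30% vs 10%: 0.00 SD.
- Dependent on baseline, intervention arm only: 0.00 SD.
- Dependent on T1, same in both arms: within 0.005 SD of zero.
- Dependent on T2 itself, same in both arms: 0.00 SD.
- Dependent on unseen T2, intervention arm only: 0.18 SD (T0–T2 correlation 0.6).

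In the last pattern a likelihood analysis using T0 and T1 still leaves 0.11 to 0.15 SD. At 1.5 logits per SD it leaves 0.13 to 0.17, against 0.22 to 0.26 for ANCOVA.

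**5. Illustration for the next trial** (two-sided 5%, 80% power; all values assumed). The approximate formula is n per arm = 2(1.960 + 0.842)²/d² = 15.70/d². A true d of 0.30 needs 15.70/0.09 = 174.4, so 175. An observed d of 0.40, which is 0.10 too large, gives 15.70/0.16 = 98.1, so 99.

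**The case against.** **The article never says complete-case.** A reader might infer that the plan is a completer analysis and so flatly contradicts its own claim. The text does not support that. Imputation before ANCOVA would fit every word of it and may stand in a fuller document that is not shown. A missing-data method left to that document is no finding. What stands is narrower: the article states a property and names a method that does not deliver it unaided. That method also leaves unused a score the trial collects.

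**The sentence may only be about grouping.** On that reading ANCOVA complies for carers who stop the modules but answer. That is right, and those carers are not at issue. The reading does not cover carers with no score.

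**The bias needs a chosen mechanism.** A reader might infer that ANCOVA will show a benefit where none exists. The article gives no information on the size, direction or cause of dropout, and several patterns give no bias. If distressed controls leave instead, the sign reverses. The 0.07 to 0.14 SD is also smaller than one standard error, about 0.17.

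**The comparison favours the mixed model.** It does: when dropout depends on T1, a method using T1 is unbiased by construction. With dropout on unseen T2 it only reduces the bias, and the gain in precision is slight. A carer with T0 alone is included in name but adds no follow-up information.

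**The stakes are modest.** The effect sizes may inform a sample size alongside earlier studies. This limits the harm to a planning input but does not remove it.

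**Conclusion.** The point holds in a limited form. As named, ANCOVA leaves out carers without the follow-up score, up to 23 of 120 within the retention criterion, and discards T1 for those who miss T2. The resulting bias in the effect size is conditional: it requires loss that differs by arm and depends on distress after baseline. Its size is about 0.07 to 0.14 SD in either direction when T2 dropout depends on T1 in one arm only, with retention near 70% vs 91% and correlations of 0.5 to 0.8, all of which are assumed. It is about zero for random, baseline-dependent or symmetric dropout. No bias in the SDs has been shown. The change is worth making because the better method uses data and software already in the plan.

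**What to change.** For each scale, replace ANCOVA with one likelihood-based mixed model for repeated measures in SPSS MIXED. Use T0, T1 and T2 as responses, arm-by-time terms, baseline means constrained equal between arms, and an unstructured covariance. Report the T1 and T2 differences between arms with 95% confidence intervals. Every randomised carer with any score then enters the model.

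Because this reduces but does not remove bias from dropout that depends on unseen T2 scores, add one simple missing-not-at-random sensitivity analysis at T2.

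If ANCOVA is kept without imputation, describe it as a complete-case analysis by assigned group.

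The cost is analysis wording and slightly more analysis work: six scores (three DASS-21 subscales, WEMWBS, Resilience Scale, SCS-R), with no extra participants, visits or software.

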## Discussion

Interventions for family carers with a training and support component have been shown to be effective in reducing levels of stress and improving quality of life [7–9]. However, these interventions are often delivered face to face, which can be a barrier to some family carers’ participation [10]. The online delivery of the current intervention offers flexibility, removing these barriers [11, 12] and encouraging and promoting participation. Despite the potential benefits of the Carers-ID intervention, its feasibility is unknown.

The Carers-ID intervention was co-designed with family carers of people with ID and voluntary sector partners and is therefore directly relevant to their lives. Our initial testing has shown that the programme is acceptable to family carers who felt that providing peer support and the opportunity to talk to other carers was an important element of the work. However, our use of convenience sampling in the absence of a sampling frame from which to draw a list of eligible participants may mean that our sample lacks representativeness to the wider population of family carers of people with ID. We intend to address this issue by recruiting from across the four countries of the UK and providing all who are interested in taking part with the opportunity to do so.

The mixed-methods design in the current study will provide important information on the feasibility of the Carers-ID online intervention. It will provide us with useful data on how our chosen outcome measures perform while also contributing information on the mental health of family carers. Findings from this trial will inform the appropriateness of progression to a phase III effectiveness trial, in addition to offering further recommendations to the content of the intervention, if required.

## Data Availability

The authors confirm that data sharing is not applicable to this article as no new data were created or analysed in this manuscript.

## Abbreviations

CONSORT: Consolidated Standards of Reporting Trials
DASS-21: Depression, Anxiety and Stress Scale-21
ID: Intellectual disabilities
MRC: Medical Research Council
SCS-R: Social Connectedness Scale Revised
UK: United Kingdom
WEMWBS: Warwick–Edinburgh Mental Well-being Scale
